## **12. QUALITY ASSURANCE AND CONTROL**

### **12.1 Data handling and record keeping / archiving**

#### **12.1.1 Case Report Forms**

All study data will be entered in an Electronic Data Capture (EDC) system by the study nurse or study coordinator or investigator or the local data manager with no double data entry.

CRFs will be kept current to reflect subject status at each phase during the course of the study. Study-related data of the patient will be collected in a coded manner. The names of the patients will not be disclosed. A code (unique) will be attributed to each patient registered.

Persons authorized by the sponsor-investigator to perform data entry or data review will be communicated to the data manager who will provide individual access codes according to the function assigned. CRF data entry authorization will be documented on each delegation log and a list of all authorized persons and their function stored with the data manager.

#### **12.1.2 Source data**

Source data must be available at each site to document the existence of the study participants. Source data must include the medical history and treatment of the participant as well as the original documents relating to the study:

- worksheets (as paper CRF) for screening, baseline, week2, week6, week 12, week24, week 36, week 48 visits and extra visit, study drug discontinuation visit and study discontinuation visit);
- logs (adherence log, drug accountability log, adverse event log, concomitant medication log);
- patient diary;
- cost-related letter from the patient's health insurance company.

The following data will be considered as source documents: patient questionnaires, demographic data, visit dates, participation in study and Informed Consent Forms, SAEs, AEs, adherence log, drug accountability log and concomitant medication log. All other data must be available in the participant's hospital chart.

#### **12.1.3 Analysis and Record keeping / archiving**

At interim safety analysis and final analysis, data files will be extracted from the database into statistical packages to be analyzed. The status of the database at this time is recorded in special archive tables.

The study database with all archive tables will be securely stored by the CTU, University of Bern. Essential documents, the trial master file as well as the investigator file for Geneva will be stored at the HIV unit, infectious diseases consultation at the HUG. Investigator files of other Swiss sites will be stored at each site separately. All study data must be archived for a minimum of 10 years after study termination or premature termination of the clinical trial.

## **12.2 Data management**

### **12.2.1 Data Management System**

The CRFs in this trial are implemented electronically using a dedicated electronic data capturing (EDC) system (secuTrial). The EDC system is activated for the trial only after successfully passing a formal test procedure. All data entered in the CRFs are stored on a Linux server in a dedicated Oracle database.

Responsibility for hosting the EDC system and the database lies with CTU, University of Bern.

### **12.2.2 Confidentiality, Data Protection (Data security, access and back-up)**

The server hosting the EDC system and the database is kept in a locked server-room. Only the system administrators have direct access to the server. A role concept with personal passwords (site investigator, statistician, monitor, administrator etc.) regulates permission for each user to use the system and database as he/she requires.

All data entered into the CRFs are transferred to the database using Secure Sockets Layer (SSL) encryption. Each data point has attributes attached to it identifying the user who entered it with the exact time and date. Retrospective alterations of data in the database are recorded in an audit table. Time, table, data field and altered value, and the person are recorded (audit trail). A multi-level back-up system is implemented.

#### **12.2.3 Electronic and Central Data Validation**

Data is checked by the EDC system for completeness and plausibility. Furthermore, selected data points are cross-checked for plausibility with previously entered data for that participant. In addition, central data reviews will be performed on a regular basis to ensure completeness of the data collected and accuracy of the primary outcome data.

Before database lock the PI will validate the collected data with his signature.

### **12.3 Monitoring**

For quality control of the study conduct and data retrieval, all study sites will be visited on-site by appropriately trained and qualified monitors. Any findings and comments will be documented in site visit reports and communicated to the local Investigator and to the Sponsor as applicable. Investigators at the participating study sites will support the Monitor in his/her activities. Prior to study start (first participant enrolled) a plan detailing all monitoring-related procedures will be developed. All source data and relevant documents will be accessible to Monitors and questions of Monitors are answered during site visits.

### **12.4 Audits and Inspections**

No audits are foreseen by the sponsor-investigator. The study documentation and the source data/documents are accessible to auditors/inspectors (also CEC and CA) and questions are answered during inspections. All involved parties must keep the participant data strictly confidential.

### **12.5 Confidentiality, Data Protection**

Direct access to source documents will be permitted for the purposes of monitoring, audits and inspections. Both ethics committee members and employees must also understand the confidentiality requirements for any information divulged to them. The data generated by this study will be considered confidential by the investigators, except to the extent that it is included in a publication as agreed in the publication policy of this protocol.

All data will be collected without any names and identifying information will not be recorded in transcription of tapes.

The protocol will be accessible to the trial team and all investigators and delegates during and after the course of the study. The dataset will be accessible only to the data manager, the principal investigators, sponsor-investigator and the statistician.

### **12.6 Storage of biological material and related health data**

Plasma samples will be stored until at least the publication of the final manuscript

### 13. POST-STUDY

The study period ends at the week 48 visit or at the study discontinuation visit.

#### **Antiretroviral treatment and monitoring after the end of the study period**

At week 48 or study discontinuation visit, all patients will be offered the possibility to continue their treatment with DTG + FTC dual therapy, or previous-to-study cART regimen, or current cART regimen, or another regimen. This will be decided at the end of study by treating physician in collaboration with the patient. We suggest planning a viral load follow-up 6 weeks after an ARV de-escalating switch or a switch to a different regimen from the previous-to-study cART.

At week 48 or study discontinuation visit, all patients will be offered the possibility to continue their follow-up as standard monitoring or with one or more options from the patient-centered monitoring, according to local possibilities.

The treating physician will schedule follow-up after the end of the study period in any case, from the following cases:

- AE, SAE, SUSAR still ongoing (see point 10.1.3);
- Pregnancy still ongoing (see point 10.1.2 and 10.1.3);
- HIV-RNA  $\geq 20$  cp/ml, for which the procedure described at point 3.6 applies.

#### **Post-study visits**

All subjects having concluded the week 48 study visit will give their informed consent to extend the study follow-up to 3 years with one visit per year (i.e. week 96 and 144 visits) coinciding with a standard-of-care follow-up visit.

Visit 96 and 144 (+/- 30 days)

##### *Clinical assessments:*

- ART changes since previous visit and reasons for changes;
- Current treatment satisfaction;
- Monitoring options changes since previous visit and reasons for changes;
- Current monitoring satisfaction;
- Number, date and value of HIV-RNA performed since previous visit;
- Number, date and results of genotypes resistance testing performed since previous visit\*;
- Grade 3 or 4 AE, SAE and pregnancy occurrence since previous visit (reported yearly);
- Quality of life questionnaire and visual analogues scale;
- Adherence questionnaire\*;
- Patient's weight and blood pressure\*.

##### *Laboratory assessments:*

- HIV-1 RNA in plasma\*;
- CD4 count\*;
- Full blood count\*;
- Safety serum chemistry\*: creatinine, ASAT/ALAT, alkaline phosphatases, glucose and lipid profile.

---

\* Data will be extracted from the SHCS database whenever possible.

*Table of post-study procedure and assessments:*

|                                                                                                  | Week 96 (+/- 30days) | Week 144 (+/- 30 days) |
|--------------------------------------------------------------------------------------------------|----------------------|------------------------|
| ART changes since previous visit and reasons for changes                                         | X                    | X                      |
| Current treatment satisfaction                                                                   | X                    | X                      |
| Monitoring options changes since previous visit and reasons for changes                          | X                    | X                      |
| Current monitoring satisfaction                                                                  | X                    | X                      |
| Number, date and value of HIV-RNA performed since previous visit                                 | X                    | X                      |
| Number, date and results of genotypes resistance testing performed since previous visit*         | X                    | X                      |
| Grade 3 or 4 AE,SAE and pregnancy occurrence since previous visit (reported yearly)              | X                    | X                      |
| Quality of life questionnaire and visual analogues scale                                         | X                    | X                      |
| Adherence questionnaire*                                                                         | X                    | X                      |
| Patient's weight and blood pressure*                                                             | X                    | X                      |
| HIV-1 RNA in plasma*                                                                             | X                    | X                      |
| CD4 count*                                                                                       | X                    | X                      |
| Full blood count*                                                                                | X                    | X                      |
| Safety serum chemistry*: creatinine, ASAT/ALAT, alkaline phosphatases, glucose and lipid profile | X                    | X                      |

\* Data will be extracted from the SHCS database whenever possible

### **Objectives and Outcomes**

The overall objective of the post-study is to evaluate the long term efficacy, feasibility and acceptance both of the DTG+FTC dual strategy and of the options of a patient-centered monitoring as an observation without any intervention.

Secondary Outcomes related to the post-study:

1. Proportion of patients maintaining HIV suppression;
2. Proportion of patients experiencing loss of future drug options;
3. Time to loss of virological response (TLOVR);
4. Change in CD4 cell count from;
5. Change in lipidic profile;
6. Change in glucose profile;
7. Change in Framingham-calculated cardiovascular risk;
8. Change in glomerular function rate;
9. Proportion of patients with an adverse event of grade 3 or 4;
10. Proportion of patients with a severe at least one serious adverse event (SAE);
11. Proportion of patients with a CNS adverse event;
12. Changes in patient weight;
13. Change in patients' health-related quality of life;
14. Assessment of ART changes during post-study;
15. Assessment of patient's treatment satisfaction;

16. Assessment of option for monitoring changes during post-study;
17. Assessment of patient's monitoring satisfaction;
18. Number of viral load performed yearly;
19. Patient adherence to treatment.

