| Measurements and procedures: | 
Intervention: DTG 50mg 1x / day + FTC 200 mg 1x / day
 
Clinical procedures: participants will be screened up to 4 weeks prior to the baseline visit and, if eligible, will be seen at the baseline visit, at week 6 and week 12, and twelve-weekly afterwards (weeks -4, 0, 6, 12, 24, 36 and week 48). During each of these visits starting from the baseline visit, adherence to study drug will be assessed, concomitant medications and adverse events will be evaluated.
 
Laboratory procedures: besides HIV viral load performed at each study visit, the following laboratory assessments will be performed for all patients:
 
 
• Screening visit: CD4 count, full blood count, safety serum chemistry, glucose and lipid profile;
 
• Baseline visit: HIV-DNA level in peripheral blood;
 
• Week 48: HIV-DNA level in peripheral blood, CD4 count, full blood count, safety serum chemistry, glucose and lipid profile, DTG and FTC plasma concentration for patients receiving DTG and FTC);
 
• Beta HCG (urinary pregnancy test) at screening visit and every 6 months thereafter (i.e. week 24 and 48 visits) in women of childbearing potential;
 
• DTG + FTC concentration in plasma for patients taking DTG and/or FTC in case of HIV-RNA <math>\geq</math> 100 copies/ml (if HIV-RNA is
 
                                                                                                                                                                                                                                                                                                                                                                                                                            |

 HBV-susceptible subjects will be offered with immunization as standard-of-care practice.

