### 3.7 Risks / Benefits

The main risk in this trial is virological failure on DTG + FTC dual therapy. In the ART Cohort Collaboration of 18 cohorts from Europe and North America including about 17900 patients, low level viremia measured between 50 and 199 copies/ml was weakly associated with virological failure (aHR 1.38, 95%CI 0.96-2.00) (85). We will measure HIV-1 RNA level in the plasma on a regular basis to monitor for low level viremia. Any patient with HIV-1 RNA  $\geq 100$  copies/ml will undergo an additional HIV-1 RNA measurement 14 days later ( $\pm 5$  days), as well as additional adherence session and review of concomitant medications and dolutegravir and emtricitabine plasma concentration measurements.

We will define virological failure as plasma HIV-1 RNA  $\geq 100$  copies/ml on two consecutive measurements. Any patient reaching virological failure will be assessed for genotypic resistance and pharmacogenetic analyses. This latest analysis will be only done in patients who are included in the SHCS and have also signed a consent form for genetic studies. In case of virological failure, the patient will undergo an additional medical visit with review of adherence, concomitant medications, discussion of results of DTG + FTC plasma concentration. Patients randomised in the DTG + FTC dual therapy arm will be switched to a standard cART regimen while waiting for results of genotypic resistance. Patients randomised in the continuing cART arm will await results of the genotypic results. In both cases, treatment will be adjusted according to genotypic resistance results. All failing patients will complete study procedures until week 48. Figure 3 presents the algorithm for the management of virological failure.

Any patient with HIV-RNA between 20 and 99 copies at any time of scheduled visits will have an additional HIV-RNA measurement after 6 weeks (+/-5 days).

Figure 3: Algorithm for the management of virological failure

[figure not shown]

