## **6. STUDY DESIGN**

### **6.1 General study design and justification of design**

This is a pragmatic multicentre, 2 x 2 factorial randomized controlled trial with 1:1:1:1 randomization to switching to DTG + FTC dual therapy or continuation of cART and to patient-centered monitoring or continuation of standard monitoring (Figure 4).

[figure not shown]

Figure 4: Schematic presentation of study design DTG + FTC dual therapy

HIV-infected patients virologically suppressed for at least 24 weeks on standard cART will be randomly allocated:

- Standard-of-care arm: patients randomized in this arm will continue their current cART regimen, according to section 7.1.
- Dual therapy arm: patients randomized in this arm will be switched to DTG + FTC dual therapy. DTG 50 mg and FTC 200 mg will be administered once daily as dual therapy for a duration of 48 weeks.

For all patients, HIV-RNA measurements will be performed at screening, baseline, week 6, week 12, and every 12 weeks afterwards. Any patient with HIV-RNA between 20 and 99 copies/ml at any time of scheduled visits will have an additional HIV-RNA measurement after 6 weeks ( $\pm 5$  days). Any patient with HIV-RNA  $> 100$  copies/ml at any time of scheduled visits will have an additional HIV-RNA measurement after 2 weeks ( $\pm 5$  days).

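### After week 48 viral-load testing thins to one mandated test a year with no mandated repeat, yet the two-value TLOVR analysis is carried on to weeks 96 and 144, where events are likely to be missed or dated late

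*Protocol*

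**What the plan says.** **To week 48.** Section 6.1 states that "HIV-RNA measurements will be performed at screening, baseline, week 6, week 12, and every 12 weeks afterwards". The synopsis gives the same schedule, "twelve-weekly afterwards (weeks -4, 0, 6, 12, 24, 36 and week 48"), with viral load taken at every visit ("besides HIV viral load performed at each study visit"). Section 3.7 adds repeats: a patient at or above 100 copies/ml "will undergo an additional HIV-1 RNA measurement 14 days later", and one between 20 and 99 is retested after 6 weeks.

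**After week 48.** Under Post-study visits in section 13, consenting patients "extend the study follow-up to 3 years with one visit per year (i.e. week 96 and 144 visits"), each with a window of 30 days either side and one HIV-RNA. These visits also collect "Number, date and value of HIV-RNA performed since previous visit". Section 8.2.1 says regular cohort monitoring resumes after the study, without giving a viral-load frequency. The retest procedure is carried over only for HIV-RNA of 20 copies/ml or more at the end of the study period. For patients who change treatment, section 13 says "We suggest planning a viral load follow-up 6 weeks after an ARV de-escalating switch", or after a switch to a regimen other than the pre-study one.

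**Outcomes and analysis.** Section 13 lists suppression (item 1), "Time to loss of virological response (TLOVR") (item 3) and the yearly number of viral loads (item 18), with no new definitions. Its statistical paragraph applies section 11 to weeks 96 and 144. Section 11.4.2 analyses TLOVR by Kaplan-Meier and Cox regression. Section 5.2 defines it, up to week 48, as the first of two confirmed values above 100 copies/ml at least two weeks apart.

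**The concern.** A confirmed-failure endpoint depends on how often patients are tested and on whether a high value is repeated. Both are fixed by protocol to week 48, and neither is fixed afterwards. A Kaplan-Meier curve drawn through week 48 to week 144 would therefore mix a change in ascertainment with any change in efficacy. A flatter curve after week 48 could mean durable suppression, or simply fewer and unrepeated tests.

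Long-term efficacy is the stated purpose of the post-study phase, and the German, French and Italian summaries look to the 144-week follow-up to answer the efficacy question. The TLOVR curve is a natural display for that claim. Testing may also follow treatment choice: a patient who leaves triple therapy for dual therapy at week 48 meets the suggestion of an extra test, while one who simply stays on dual therapy does not.

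**Working it through.** The protocol states no figure to reproduce here, so the check is a count of tests followed by an illustration.

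**Mandated tests**
- Baseline to week 48: weeks 6, 12, 24, 36 and 48, so 5 in 48 weeks.
- Week 48 to week 144: weeks 96 and 144, so 2 in 96 weeks, or 1 per 48 weeks.
- Ratio: 5 to 1.

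**Share of viraemic episodes that meet the two-value rule**

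Assumptions, none of them from the protocol: viraemia starts at a uniformly distributed time, lasts D weeks (12, 24 or persistent), and routine tests after week 48 come every 24 or every 12 weeks. Let g be the gap between tests and w the wait from onset to the next test.
- With a 2-week repeat, an episode counts if w + 2 < D, so the share within a gap is min(1, (D − 2)/g).
- Without a repeat, the next routine test must also be positive, so w + g < D. The share is (D − g)/g, held between 0 and 1, and is 0 in the last gap because no later test is collected.

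In-study (gaps 6, 6, 12, 12, 12, with repeats):
- D = 12: (6 + 6 + 10 + 10 + 10)/48 = 42/48 = 87.5%.
- D = 24 or persistent: 48/48 = 100%.

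Post-study, mandated tests only, no repeat (two gaps of 48):
- D = 12 or 24: 0%.
- Persistent: 48/96 = 50%.

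Post-study, 6-monthly routine tests, no repeat (four gaps of 24):
- D = 12 or 24: 0%.
- Persistent: 72/96 = 75%.

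Post-study, 3-monthly routine tests, no repeat (eight gaps of 12):
- D = 12: 0%.
- D = 24 or persistent: 84/96 = 87.5%.

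Post-study, 3-monthly routine tests with repeats except at week 144:
- D = 12: 7 × 10/96 = 72.9%.
- D = 24 or persistent: 84/96 = 87.5%.

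| Schedule | D = 12 wk | D = 24 wk | Persistent |
|---|---|---|---|
| In-study | 87.5% | 100% | 100% |
| Post-study, mandated only | 0% | 0% | 50% |
| 6-monthly, no repeat | 0% | 0% | 75% |
| 3-monthly, no repeat | 0% | 87.5% | 87.5% |
| 3-monthly with repeats | 72.9% | 87.5% | 87.5% |

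Every post-study row lies below the in-study row, but by very different amounts. For persistent viraemia the whole shortfall comes from the last gap: the episode is seen at week 144 but has no second value.

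**Suppression.** Fewer tests give fewer chances to record a high value. Against that, section 5.1 forgives a blip below 200 copies/ml only if a value below 50 follows, so a value of 100 to 199 at the last visit stays a failure. The missing-as-failure rule in section 11.5, if carried over, also adds failures. The net direction cannot be settled.

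**The case against.** The strongest reply is that the endpoint does not rest on one test a year. All interim HIV-RNA values are collected with dates, cohort monitoring continues, and the yearly test count is itself an outcome. This stands, and it rules out the stronger reading that a reader might infer, namely that losses of response must fall after week 48 whatever the drug does. With 3-monthly tests and repeats the fall is modest. What remains is that neither the frequency nor the repeat is fixed, so the protocol cannot say which row of the table applies.

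Second, section 13 carries over the methods of section 11, while the definitions sit in section 5 and are worded for week 48. Carry-over of the definitions is thus an inference. It is the natural one, since no other TLOVR definition is given, but it is not stated. A statistical analysis plan may refine this; the protocol itself nevertheless fixes the method at weeks 96 and 144.

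Third, a reader might extend the point to suppression or to a bias between arms. The documents support neither. The direction for suppression is unclear, and section 11.4.2 already includes a snapshot analysis. The mandated post-study visits are the same in all arms, and the suggested extra test is not tied to allocation. Testing could differ by arm, but no bias is shown.

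Finally, these are secondary outcomes of an observational extension. That limits the weight of the point without removing it.

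**Conclusion.** The point holds for TLOVR after week 48. Mandated testing drops five-fold, no repeat is mandated for new viraemia, and a two-value endpoint is still to be analysed by Kaplan-Meier and Cox methods at weeks 96 and 144. Events are likely to be under-detected or dated late. The size depends on routine testing: for an assumed 12-week viraemia the confirmed share goes from 87.5% in-study to between 0% and 73%, and for persistent viraemia from 100% to between 50% and 87.5%. These figures rest on assumed durations, uniform onset and assumed routine schedules. One conclusion needs none of those assumptions: viraemia first seen at week 144 has no later planned visit to collect its confirmation.

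The week-48 primary non-inferiority analysis is untouched. This is an inexpensive improvement to the long-term analysis, not a threat to the main result.

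**What to change.** In the outcomes and statistical paragraphs of section 13:
- End the confirmatory Kaplan-Meier/Cox analysis of TLOVR at week 48.
- Show weeks 48 to 144 separately as an interval-censored analysis that uses all dated HIV-RNA values, and state in advance how a single unconfirmed value is counted, in particular at week 144.
- Report tests per patient-year by arm beside it, from item 18.
- Make the snapshot on the HIV-RNA in the visit window (30 days either side) the main suppression measure at weeks 96 and 144, in place of the 3-week window written for week 48 in section 9.2.2.

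The sponsor should also reconcile the cross-reference in section 13: it sends the reader to point 3.6 for the retest procedure, but 3.6 deals with the choice of comparator and the procedure is described in 3.7. Whether any clinical retesting rule applies after week 48 is for the sponsor to state.

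The cost is wording only, with no new data. The downside is a coarser long-term outcome.
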